### Patient discontinuation criteria

2.10

Patient must be discontinued from the trial for any of the following reasons:

Enrollment into the trial revealed inappropriateConfirmed radiographic disease progressionMeeting the protocol specified criteria for discontinuation in phase I and II studyUnacceptable severe adverse events at the discretion of the investigatorThe patient withdraws consent for treatment due to adverse eventsThe patient withdraws consent for treatment for any reason other than adverse eventsInvestigator's decision to withdraw the subject

### Statistical analysis

2.11

Statistical analyses and reporting will be conducted in accordance with the Consolidated Standards of Reporting Trials guidelines, with the primary analyses based on the intent-to-treat principle without imputing any missing observations. All efficacy analyses will be based primarily on the full dataset, which includes all patients who have received at least one dose of pembrolizumab and imatinib mesylate and were in accordance with the study protocol. Safety analysis will be conducted using data from the safety analysis population. For baseline variables, summary statistics will be performed using frequencies and proportions for categorical data and means and standard deviations for continuous variables. The primary efficacy endpoint of the study is ORR after 4 cycles from baseline, considering a response threshold of 5% (H_0_, null hypothesis) and an expected response rate of 30% (H_1_, alternative hypothesis). A minimum of 14 patients are required to achieve a 10% two-sided type I error and 80% power based on the exact binomial distribution. A phase II target sample size of 16 was set to account for an expected patient dropout of 10%. Together with maximum sample size of phase I, a total of 22 patients will be expected. All statistical analyses will be performed using SAS software version 9.4 (SAS Institute).

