### Study design

2.2

The phase I study is a dose-escalation study comprising two dose levels of imatinib mesylate (200 and 400 mg/day, respectively) with fixed dose of pembrolizumab (200 mg every 3 weeks) to evaluate safety and tolerability and identify maximum tolerated dose/administered, and determine recommended phase II dose (RD).

In phase II study, a Simon's minimax two-stage design is employed to test the null hypothesis of a 5% RR vs 30% alternative (1-sided α 0.05, power 80%, ≥1/7 RR to continue to total of 3 ≥ 14). The treatment period with the combination therapy of both studies will continue every 21 days for up to 33 cycles (∼2 years) as long as patients are receiving benefit from treatment and have not had disease progression or met any criteria for study withdrawal.

The trial design is depicted in Figure 1.

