### Treatment in phase I study

2.7

Phase I study is 3+3 dose-escalation study comprising two dose levels of imatinib mesylate with fixed dose of pembrolizumab. This study will be broken into 2 levels of 3 to 6 patients each level. The cycle length of regimen is 21 days. Each patient will receive 2 cycles of imatinib mesylate and pembrolizumab combination therapy and assessed for DLT at day 42 (±2). The first level (Level 1) of patients will receive the lowest dosing regimen, oral imatinib mesylate 200 mg quaque die (QD) for 21days and intravenous pembrolizumab 200 mg on day1 every 21 days, with subsequent cohorts receiving increasing doses of imatinib mesylate, 400 mg QD. After the RD has been determined, this dosage scheme will be used to treat patients in phase II study. If patients in phase I show no DLTs followed by non-progressive disease, they will continue with combination therapy for up to 2 years.

Escalation scheme is as follows (Fig. 1):

1.If DLT is not observed in all 3 cases in Level 1, proceed to enrollment of Level 2.2.If DLT is observed in one of 3 cases in Level 1, add further 3 cases, anda.If DLT is observed in 1 of total 6 cases, proceed to enrollment of Level 2.b.If DLT is observed 2 or more of 6 cases, the study is discontinued.3.If DLT is observed 2 of 3 cases in Level 1, the study is discontinued.Regarding the transition to Level 2, the evaluation of the investigator will be discussed and judged by Efficacy and Safety Evaluation Committee.4.If DLT is not observed in all 3 cases in Level 2, dose of Level 2 is determined as RD.5.If DLT is observed in one of 3 cases in Level 2 cohort, add further 3 cases, anda.If DLT is observed in 1 of total 6 cases, dose of Level 2 is determined as RD.b.If DLT is observed 2 or more of 6 cases, dose of Level 1 is determined as RD.6.If DLT is observed 2 of 3 cases in Level 2, dose of Level 1 is determined as RD.The evaluation of the RD by the investigator will be discussed and judged by Efficacy and Safety Evaluation Committee.

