### Treatment in phase II study

2.9

A sample size of 7 in each stage of the 2-stage design is required to detect efficacy. Eligible patients receive the dose determined in phase I cohort. The subject of the efficacy evaluation includes those who received treatment with RD in the phase I study. The cycle length of regimen is 21 days. Each patient will receive 4 cycles of imatinib mesylate and pembrolizumab combination therapy and assessed for clinical efficacy at week 12 (±7 days) at the site per RECIST 1.1. After evaluating 7 patients for response in 4 cycles of the first stage, the trial would be terminated if no patient had a CR, PR. If at least one patient met these criteria, an additional 7 patients would be enrolled for the second stage. A total of 14 (16 at maximum) patients including those who received treatment with RD in the phase I study will be assessed. At the end of the trial, if the total number of responses (CR + PR) is 3 or more, the combination would be considered promising. Each patient who shows non-PD, they are allowed to continue with combination therapy for up to 2 years. Patients will be assessed for response criteria every 4 cycles.

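### The primary ORR is called intent-to-treat but is restricted to protocol-compliant patients with no imputation, so treated patients without a week-12 result can leave the denominator and raise the estimate

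*Protocol article*

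**What the plan says.** All places are in the protocol article.

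- **Principle and missing data (Statistical analysis, 2.11).** The section describes the "primary analyses based on the intent-to-treat principle without imputing any missing observations".
- **Analysis set (2.11, next sentence).** Efficacy analyses rest primarily on "all patients who have received at least one dose of pembrolizumab and imatinib mesylate and were in accordance with the study protocol".
- **Timing (Treatment in phase II study, 2.9).** Each patient is "assessed for clinical efficacy at week 12 (±7 days) at the site per RECIST 1.1" after 4 cycles. Later assessments follow every 4 cycles, and no earlier efficacy scan is described.
- **Decision rule (Study design, 2.2, and 2.9).** The design is summarised as "1-sided α 0.05, power 80%, ≥1/7 RR to continue to total of 3 ≥ 14". Section 2.9 gives the final rule as 3 or more CR or PR, with 14 and at most 16 patients assessed. The Abstract adds that the lower limit of a two-sided 90% interval must exceed the threshold rate.
- **Dropout (2.11).** "A phase II target sample size of 16 was set to account for an expected patient dropout of 10" per cent.
- **Phase I patients (Endpoints, 2.6, and 2.9).** Those treated at the recommended dose (RD) enter the efficacy evaluation.

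**The concern.** The two adjacent sentences in 2.11 do not describe one population. Intent-to-treat keeps patients regardless of later compliance; a condition that they followed the protocol removes some because of what happened after entry. The no-imputation clause adds a second way out, because a patient with no week-12 result has no value to enter.

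This matters because the primary endpoint is read at a single time point. Section 2.10 lets patients leave for toxicity, withdrawn consent or investigator decision, and some may die or deteriorate before week 12. In a response-rate analysis these are ordinarily failures. If they are treated as missing instead, the denominator shrinks while the count of responders stays the same. With 14 to 16 patients, one or two exclusions visibly change the result. In an open-label, single-arm, site-assessed trial, a denominator that the text does not settle can also be chosen after responses are known.

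**Working it through.** **1. The plan's own design reproduces.** Inputs from 2.2, 2.9 and 2.11: null rate 5%, alternative 30%, stop at 0/7, success at 3 or more of 14. The success probability is the sum over x = 1 to 7 of P(X₁ = x) × P(X₂ ≥ 3 − x), with X₁ and X₂ each binomial(7, p).

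- p = 0.05: 0.027 (target at most 0.05).
- p = 0.30: 0.810 (target 0.80).
- Dropout: 14/(1 − 0.10) = 15.6, rounded up to 16.

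The sample size is sound.

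**2. Effect on the estimate.** Let d be the share of treated patients who have no week-12 result and are all non-responders (the extreme case). The complete-case ORR is p/(1 − d). Only d = 10% comes from the plan; the other values are assumed, to show the range.

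| d | True 30% reads as | True 5% reads as |
|---|---|---|
| 5% | 31.6% | 5.3% |
| 10% (plan) | 33.3% | 5.6% |
| 20% | 37.5% | 6.3% |
| 30% | 42.9% | 7.1% |

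**3. The same in patients.** Take 3 responders among 16 treated, two of whom have no scan.

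| Denominator | ORR | Exact two-sided 90% interval |
|---|---|---|
| All 16 treated | 18.8% | 5.3% to 41.7% |
| 14 with a scan | 21.4% | 6.1% to 46.6% |

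**4. Effect on the false-positive rate.** Success is a count of responders, and dropping non-responders creates none. With at most 16 treated and a true all-treated rate of 5%:

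- P(3 or more of 16), ignoring the stage-1 gate: 0.043.
- P(3 or more of 16 and at least 1 of the first 7): 0.037.

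The interval rule in the Abstract offers no practical way round this. Two responders clear 5% only with 7 or fewer in the denominator: the lower limit is 5.3% for 2/7 and 4.6% for 2/8. More than half of 16 patients would have to be excluded.

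**5. Operating characteristics if all 16 treated patients are kept.** Rule: at least 1/7, then at least 3/16.

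- The lower 90% limit for 3/16 is 5.3%, above 5%. For 3/15 it is 5.7% and for 3/14 it is 6.1%.
- Type I error: 0.037.
- Power at 30%: 0.856.
- Power if 10% of patients are counted as failures, so that p = 0.30 × 0.90 = 0.27: 0.798.

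**The case against.** **The exclusion is inferred.** No sentence says that dropouts leave the denominator. Raising 14 to 16 is routine; it suggests that 14 evaluable patients are wanted but does not confirm that the others are excluded, and 2.9 speaks of up to 16 being assessed. The no-imputation clause may mean only that no response is invented, and the compliance phrase may have been meant as eligibility. The article condenses a fuller protocol (version 1.3 is mentioned). This stands as a limit on certainty. It does not remove the conflict, because the article itself states the population and the missing-data rule, and the two statements disagree.

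**Type I error.** A reader might infer that the real false-positive rate exceeds 5%. If lost patients could be replaced without limit until 14 were evaluable, the two-stage rate would be 3.6% at 10% loss, 4.8% at 20%, 6.7% at 30% and 9.7% at 40%. The last two need 14/0.70 = 20 and 14/0.60 = 23.3 treated patients, beyond the stated cap of 16. Within the cap the inference fails (step 4).

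**Heavy loss.** A reader might also take the monotherapy median PFS of 2.8 to 3.7 months in the Introduction, which under an exponential curve implies about 40% to 50% progressing by week 12, as the likely share missing. Documented progression is an observed non-response and can stay in the denominator. The plan's only figure for loss is 10%.

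**Patients not at the RD.** The sentence in 2.11 does not repeat the RD restriction, but 2.6 and 2.9 already bring in only phase I patients treated at the RD. Nor does "If patients in phase I show no DLTs followed by non-progressive disease, they will continue with combination therapy for up to 2 years" in 2.7 bear on the analysis set. That reading is not supported.

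**Conclusion.** The point holds as a contradiction in the primary analysis population and a likely upward bias in the reported ORR and its interval. At the plan's own 10% loss the size is modest: up to 3.3 percentage points on a true 30%, or 18.8% against 21.4% in the 16-patient example. These are upper figures, since they assume that every lost patient is a non-responder and is dropped. Exclusions for protocol deviations come on top; their number and direction cannot be judged from the article. The sample size and the 3-or-more rule are not at fault, and the false-positive chance stays at or below 4.3% while no more than 16 patients are assessed. The wording should still be corrected, because the current text leaves the denominator of the primary result open and the correction costs almost nothing.

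**What to change.** In Statistical analysis (2.11):

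1. Define the primary efficacy set as all patients who received at least one dose of study treatment at the RD, including phase I patients at that dose, as 2.6 and 2.9 already say.
2. Remove the protocol-compliance condition from that set and, for ORR, the no-imputation clause.
3. State that any patient without a documented qualifying CR or PR counts as a non-responder, whatever the reason, both at the stage-1 decision and at the end.
4. Report the ORR in the protocol-compliant set as a sensitivity analysis.
5. Keep the threshold of 3 or more responses for 14 to 16 patients (step 5).

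The cost is a wording change in the protocol and analysis plan, with no extra patients. The reported ORR may be slightly lower, and power at 16 treated is 79.8%, just under the nominal 80%, if 10% are counted as failures.

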## Discussion

3

This is an open-labelled single-arm clinical trial of the use of imatinib mesylate and pembrolizumab combination therapy for Japanese metastatic *KIT*-mutated melanoma patients who failed ICIs treatment. The rationale of this study relies on the several previous clinical and basic evidence showing the enhancement of the antitumor activity by KITi administration. KITi promoted immune responses by selectively reducing the immunosuppressive monocytic MDSC and by restoring CD8+ and CD4+ T-cell populations in mice.^[13]^ Furthermore, it was recently reported that anti-PD-1 therapy response in melanoma patients is modulated by the presence of tumor-infiltrating mast cells and that combining anti-PD-1 therapy with imatinib resulted in the depletion of mast cells and complete regression of tumors in humanized-mouse melanoma model.^[14]^ Clinically, one case report has shown that metastatic mucosal melanoma of the vulva harboring *KIT* mutation showed response to sequential administration of imatinib mesylate after anti-PD-1 antibody.^[15]^ In addition, another report showed that co-administration of imatinib mesylate and pembrolizumab in an anti-PD-1 monotherapy failed *KIT*-mutation positive melanoma patient achieved complete remission for almost 12 months.^[16]^ Based on these clinical and biological observations, we hypothesize that imatinib mesylate and anti-PD-1 antibody combination will show a clinical benefit in *KIT*-mutant melanoma even it has resistant to ICIs therapy.

This study has several limitations. First, the number of patients is small to assess the true safety and efficacy of imatinib mesylate and pembrolizumab combination. Second, differences in the clinical response to imatinib mesylate are expected among the study participants due to the diversity of mutational status of *KIT* gene as reported in the four phase II trials of imatinib mesylate monotherapy for melanoma; ORR of melanoma patients with *KIT* mutations in exon 11 or 13 was 24.4% while that for the patients with alterations in other gene loci was 19.4%.^[17,18]^ Third, this study uses a single arm design, and therefore does not demonstrate the superiority of imatinib mesylate and pembrolizumab combination over imatinib mesylate monotherapy. Nevertheless, if the results of this study show promising efficacy and acceptable safety profile, it will contribute to the development of novel treatment option for patients with *KIT*-mutant melanoma that are refractory to standard therapy.
